## Abstract

**Background:**

Medically unexplained symptoms (MUS) constitute a major health problem because of their high prevalence, the suffering and disability they cause, and the associated medical costs. Web-based interventions may provide an accessible and convenient tool for managing MUS. We developed a personalized, Web-based, guided self-help intervention for MUS in primary care (Grip self-help) and would compare its effectiveness with that of usual care.

**Objective:**

This paper aims to describe the rationale, objectives, and design of a pragmatic randomized controlled trial (RCT) assessing the effectiveness of Grip self-help.

**Methods:**

For a pragmatic multicenter RCT, 165 adult patients with mild to moderate MUS will be recruited through general practices in the Netherlands. Randomization will be performed at general practice level. Over the course of several months, patients in the intervention group will receive a personalized set of Web-based self-help exercises, targeting the unhelpful cognitions, emotions, behaviors, and social factors that are relevant to them. The intervention is guided by a general practice mental health worker. The control group will receive care-as-usual. Primary outcome is physical health-related quality of life (RAND-36 or 36-item general health survey, physical component score). Secondary outcomes include severity of physical and psychological symptoms, mental health–related quality of life, cost-effectiveness, and acceptability. Assessments will take place at baseline, end of treatment, and at 16-, 26-, and 52-week follow-ups.

**Results:**

Recruitment started in December 2018, and enrolment is ongoing. The first results are expected to be submitted for publication in December 2021.

**Conclusions:**

To our knowledge, this is the first study to combine the concepts of electronic health, self-help, and personalized medicine in the treatment of MUS. By improving the quality of life and reducing symptoms of patients with MUS, Grip self-help has the potential to reduce costs and conserve scarce health care resources.

**Trial Registration:**

Dutch Trial Register NTR7390; https://www.trialregister.nl/trial/7390.

**International Registered Report Identifier (IRRID):**

PRR1-10.2196/13738

## Introduction

### Background

In primary care, about 50% of patients presenting with a physical complaint receive a medical diagnosis during their first visit. After extensive evaluation, approximately one-third of physical symptoms remain medically unexplained [1]. Medically unexplained symptoms (MUS) can cause significant distress and impairment for patients and are associated with high costs for society because of the resulting excess use of health care services, work absenteeism, and decreased productivity [2-4].

Although the pathophysiology of MUS is unknown, a lot has been published on factors that might trigger and maintain symptoms [5,6]. Targeting these factors, such as worries, fear, and physical inactivity, is the focus of most psychological treatments. Cognitive behavioral therapy is well studied and has shown modest improvements with regard to symptom severity and physical health–related quality of life (HRQoL) [7,8]. However, most patients with MUS are treated in primary care, and general practitioners (GPs) generally lack the time and skills to offer psychological treatment. More in general, GPs often find it difficult to treat patients with MUS [9] because of the lack of available and effective treatment options [8,10].

A recent meta-analysis has shown that self-help interventions are a promising alternative to psychological treatment for patients with MUS [11]. As self-help does not require guidance by a trained therapist, it can be easily accessible and widely available at relatively low costs, especially when offered on the Web.

### Grip Self-Help

We, therefore, developed the Web-based intervention *Grip self-help*. Grip self-help is a personalized, guided self-help intervention for patients with mild to moderate MUS in primary care. On the basis of the results of Web-based questionnaires, patients receive a personalized set of Web-based self-help exercises, aimed at the unhelpful cognitions, emotions, behaviors, and social factors that are relevant to them. The intervention has an eclectic nature and contains elements of patient education, cognitive behavioral therapy, acceptance and commitment therapy, and problem-solving treatment. As far as we know, no previous research evaluated the effectiveness of such an intervention.

### Objective

This paper describes the design of the randomized controlled trial (RCT) assessing the effectiveness of the Grip self-help intervention in general practice (Dutch Trial Register NTR7598). The primary objective of this RCT is to determine whether Grip self-help is superior to care-as-usual (CAU) for improving physical HRQoL at follow-up after 16 weeks in patients with mild to moderate MUS. Secondary objectives are as follows: to (1) assess the effectiveness of Grip self-help in comparison with CAU in improving severity of physical and psychological symptoms and mental HRQoL at follow-up after 16, 26, and 52 weeks, (2) investigate the cost-effectiveness of Grip self-help in comparison with CAU at follow-up after 16, 26, and 52 weeks, (3) assess acceptability of Grip self-help for patients and primary care professionals (PCPs), (4) investigate which patient characteristics predict effectiveness of Grip self-help, (5) investigate which characteristics of PCPs predict effectiveness of Grip self-help, and (6) investigate whether increased self-efficacy mediates treatment outcomes.

## Methods

### Study Design

This study is designed as a pragmatic multicenter randomized controlled superiority trial with 2 parallel groups and a 1:1 allocation ratio. The study protocol, intervention, participant information, and informed consent procedure have been approved by the University Medical Center Groningen Medical Ethics Committee (registration number M18.232173). The study will be conducted according to the principles of the Declaration of Helsinki (2013 version).

### Participants

Patients with mild to moderate MUS will be recruited through general practices from rural as well as urban areas in the Netherlands. Of the PCPs, 2 types will be involved in this study: GPs and general practice mental health workers (GP-MHWs). GP-MHWs are nurses, psychologists, or social workers with experience in mental health care, employed by one or several general practices. PCPs will be invited to participate through local and national GP networks, social media, and Web publicity. PCPs that show interest will be informed by a letter. If desired, more detailed information can be provided by email, telephone, or during a visit to the practice. At least 1 GP and 1 GP-MHW are required to participate for a practice to take part in the study. Participating PCPs sign an informed consent form. Subsequently, the GP selects up to 15 patients with mild to moderate MUS based on the inclusion criteria described in Textbox 1. Selected patients receive a letter with information about the study. During a telephone call with one of the researchers, additional questions from interested patients will be answered and exclusion criteria (see Textbox 1) will be evaluated. When eligible patients decide to participate in the study, they will be asked to sign an informed consent form. Next, the participant will receive an email with an invitation to fill out the baseline questionnaires in a Web-based secure environment. An overview of the study procedure is provided in Figure 1.

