#### Eligibility Criteria for Participating General Practices

*Inclusion criteria:* At least 1 GP and 1 GP-MHW from the practice take part in the study.

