### Randomization Procedure

Randomization will be performed at general practice level. After all participants from a practice have given informed consent and filled out baseline questionnaires, practices will be randomly assigned to the intervention (Grip self-help) or control (CAU) group, using Web-based randomization tool ALEA (ALEA Clinical | FormsVision). Randomization after patient inclusion prevents the possibility of recruitment bias (selection bias). Randomizing general practices rather than patients will avoid PCPs within a practice offering both Grip self-help and CAU, as this could cause contamination effects. Randomization will take place in blocks, randomly varying in size between 4 and 8, and a 1:1 allocation ratio.

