### Control Group

Participants assigned to the control group will receive CAU during the study period. This could include care by the GP, GP-MHW, physiotherapist, and a psychologist. After the last follow-up measurement at 52 weeks, participants assigned to the control group will be offered access to the study intervention.

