### Strengths and Limitations

Apart from these challenges, there are several strengths and limitations to the study. First, the Grip self-help intervention has a number of important strengths. As the intervention is provided in general practice, the intervention is easily accessible to a large group of patients. We hereby hope to also reach patients, who might not be willing to visit a mental health care facility to receive treatment. Also, the intervention is easy to implement in general practice because it is coherent with the current ways of working of PCPs. Strengths with regard to the study design are the follow-up period of 1 year, which allows for studying long-term effectiveness. Also, randomizing practices instead of patients will prevent contamination effects.

Of course, there are also a number of limitations to this study. First, self-selection of PCPs participating in the study may lead to selection bias, with an overrepresentation of PCPs having a special interest in either MUS or eHealth interventions. Second, the selection of patients by GPs also potentially causes selection bias. However, randomization takes place after the selection of patients, which limits this potential form of bias. Third, because of the nature of the intervention, patients, PCPs, and researchers will not be blinded to the study condition. This may lead to bias. Finally, outcome measures will be assessed using Web-based questionnaires. Although nearly all of the selected instruments were validated, traditional paper-and-pencil questionnaires were used in validation studies. This is of concern because psychometric properties might differ between different types of administration. However, several reviews have shown that Web-based testing usually produces very similar results compared with traditional testing [28,29].

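### A mental health worker shared by two participating practices can end up in both arms, so randomizing single practices does not by itself prevent contamination

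*Protocol article*

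**What the plan says.** Only the protocol article is available.

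- **Who the workers are** (Participants): GP-MHWs have a background in nursing, psychology or social work and are "employed by one or several general practices".
- **What a practice needs** (Eligibility Criteria for Participating General Practices): "At least 1 GP and 1 GP-MHW from the practice take part in the study". Nothing requires the GP-MHW to belong to that practice alone.
- **Unit of randomization** (Randomization Procedure): "Randomization will be performed at general practice level", 1:1, in blocks whose size varies between 4 and 8. The reason given is that "Randomizing general practices rather than patients will avoid PCPs within a practice offering both Grip self-help and CAU".
- **Role in the intervention arm** (Intervention Group): the GP-MHW guides Grip, has access to an online manual and may take an optional course on medically unexplained symptoms and Grip.
- **Role in the control arm** (Control Group), on what usual care may contain: "This could include care by the GP, GP-MHW, physiotherapist, and a psychologist". Controls are offered Grip only after the 52-week measurement.
- **The claim** (Strengths and Limitations), listed as a strength of the design: "randomizing practices instead of patients will prevent contamination effects".

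**The concern.** Practices are randomized so that the same professional does not deliver both conditions. The professional closest to the intervention is the GP-MHW, and this is the one professional whom the article describes as possibly working across practices. If two practices sharing a GP-MHW both enrol, they are two separate entries in the allocation list. The same person can then have the Grip manual and course for one practice and see care-as-usual patients in the other.

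At stake is the contrast between the arms. If a worker's training or experience with Grip improves the care of control patients, the arms move together and the estimated effect on the RAND-36 physical component score at 16 weeks is biased towards zero. A null result would then be harder to interpret, and the article's reassurance about contamination would not settle the matter.

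**Working it through.** **1. The plan's own figure.** The Sample Size section uses an unpaired t test with effect size 0.5, two-sided alpha 0.05 and power 0.80. This gives 63.8, rounded up to 64 per arm, so 128. With 20% dropout, 128 / 0.80 = 160. With design factor 1 + (4 − 1) × 0.01 = 1.03, 160 × 1.03 = 164.8, rounded to 165; 165 / 4 gives about 41 GPs. The figure reproduces and is not in dispute. It contains no term for contamination.

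**2. Do the statements fit together?**
- A GP-MHW can belong to more than one practice (Participants).
- A GP-MHW guides Grip (Intervention Group) and may treat controls (Control Group).
- Practices are allocated one by one (Randomization Procedure), and no section says that practices sharing a GP-MHW are allocated together.

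Following the plan as stated can therefore place one worker in both arms. The Randomization Procedure sentence speaks of professionals within a practice and is true as worded. The sentence in Strengths and Limitations drops that limit, and the conclusion no longer follows.

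**3. How often would a shared worker serve both arms?**
- *Independent 1:1 allocation, k participating practices sharing one worker.* P(both arms) = 1 − 2 × 0.5^k. For k = 2 this is 0.50, for k = 3 it is 0.75, and for k = 4 it is 0.875.
- *Two practices in the same balanced block of size b.* P(opposite arms) = (b/2) / (b − 1). For b = 4 this is 2/3 = 0.67, for b = 6 it is 3/5 = 0.60, and for b = 8 it is 4/7 = 0.57. Even block sizes are assumed, as exact 1:1 balance within a block requires.

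For a shared pair, opposite arms are thus at least as likely as the same arm.

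**4. Can the dilution be sized?** Take practices that share in pairs, and let
- s = share of practices in such pairs,
- p = probability of opposite arms (step 3),
- v = share of control patients in those practices who see the worker,
- f = fraction of the effect carried over.

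The diluted effect is then 0.5 × (1 − s × p × v × f). Only p can be derived from the article. It gives no value for s, v or f, so the direction is clear but the size is not.

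**The case against.** - **The stated rationale is true.** It concerns professionals within a practice, and that route is blocked. This stands. The overstatement is confined to the discussion sentence.
- **The situation may never arise.** It needs two enrolled practices with the same participating GP-MHW in opposite arms. Recruitment also runs through national and online channels, which do not imply linked practices. This stands: the number could be zero.
- **A rule may exist in the full protocol.** That is possible, since an article condenses. But the article states the unit, the claim and the fact that undercuts the claim, and it makes the claim without relying on any such rule.
- **Little can be carried over.** Grip is a problem profile plus exercises selected by algorithm, which controls cannot reach for 52 weeks. What a worker can carry is skill, the manual and the optional course. This stands and argues for a small effect per exposed patient.

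Two stronger readings are tempting, and the article supports neither.

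- *A definite loss of power.* A reader might assume that, say, 20% of controls are exposed and lose a sizeable part of the contrast. With p between 0.50 and 0.67, that exposure needs 0.20 / 0.67 = 30% to 0.20 / 0.50 = 40% of all practices to be in sharing pairs, with every control patient in the affected practices seeing the worker. The article says only that usual care may include such contact.
- *Standard errors that are too small because shared practices are correlated across arms.* Var(A − B) = Var(A) + Var(B) − 2 Cov(A, B). Ignoring a positive covariance between opposite arms overstates the variance of the difference, so inference is conservative, not falsely precise.

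**Conclusion.** The point holds in a limited form. The article allows a GP-MHW to work in several practices, gives that worker a role in both arms and randomizes single practices. The unqualified statement that contamination is prevented therefore fails for any practices that share a participating GP-MHW. For two such practices the chance of opposite arms is 50% under independent allocation and 57% to 67% within one block of 8 to 4.

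The bias would be towards zero, on the assumption that whatever the worker carries over helps control patients. Its size cannot be derived from the article, and it may be negligible if few or no workers are shared. The article does not show that contamination occurs, or that the sample size or the planned mixed model is wrong. This is a worthwhile, low-cost improvement to the allocation rule, together with a correction to one sentence.

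**What to change.** 1. At practice enrolment, ask whether the participating GP-MHW also takes part through another practice.
2. For practices not yet randomized, enter those sharing a GP-MHW in ALEA as one unit and use that unit as the cluster in the linear mixed model. Once linked practices are in the same arm, the worker's influence is correlation within an arm and should be modelled as such.
3. For practices already randomized (the Results section says enrolment is under way), record and report sharing. Add a sensitivity analysis that excludes practices whose GP-MHW is in both arms.
4. In Strengths and Limitations, restrict the claim to contamination within a practice, or state how shared workers are handled.

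**Cost.** One question and one allocation rule, with slightly fewer and larger clusters. At the plan's ICC of 0.01, two linked practices with 4 patients each form a cluster of 8 and a design factor of 1 + (8 − 1) × 0.01 = 1.07. Even if every practice were paired, the requirement would be 160 × 1.07 = 171.2 instead of 164.8. This assumes one participating GP per practice and the same ICC for the linked unit. The practical cost is delay: allocation waits until all patients in a practice have consented and completed baseline, so linked practices would have to wait for each other while the first one's baseline data age.

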#### Eligibility Criteria for Participating General Practices

*Inclusion criteria:* At least 1 GP and 1 GP-MHW from the practice take part in the study.

#### Eligibility Criteria for Participants

Textbox 1 presents the inclusion and exclusion criteria for participants.

Inclusion and exclusion criteria for participants.Inclusion criteriaAge ≥18 yearsPresenting with mild to moderate medically unexplained symptoms (MUS). In line with the guidelines provided by the Dutch College of General Practitioners, MUS are defined as “physical symptoms that have persisted for more than several weeks and for which adequate medical examination has not revealed any condition that sufficiently explains the symptoms” [12]. MUS are considered mild to moderate in case of (1) mild to moderate functional limitations because of the symptoms, (2) symptoms in 1, 2 (mild), or 3 (moderate) symptom clusters (gastrointestinal symptoms, cardiopulmonary symptoms, musculoskeletal symptoms, and nonspecific symptoms), and (3) symptom duration longer than expected by the general practitionerMain symptom concerns pain, gastrointestinal complaints, or fatigueAdequate command of the Dutch language, no major cognitive or visual impairmentExclusion criteriaReferred to or currently treated by a mental health professionalStart or adjusted dosage of psychotropic medication ≤3 months agoLikelihood of posttraumatic stress disorder (Trauma Screening Questionnaire ≥6 [13]), severe anxiety disorder (4-Dimensional Symptom Questionnaire or 4DSQ Anxiety ≥10 [14]), or severe depressive disorder (4DSQ Depression ≥6 [14])PregnancyEngaged in a legal procedure concerning disability-related financial benefitsNot in possession of an email account and a personal computer, laptop, or tablet with internet connection

**Figure figure1:**
[figure not shown]
Flowchart of the study procedure. GP: general practitioner.

### Randomization Procedure

Randomization will be performed at general practice level. After all participants from a practice have given informed consent and filled out baseline questionnaires, practices will be randomly assigned to the intervention (Grip self-help) or control (CAU) group, using Web-based randomization tool ALEA (ALEA Clinical | FormsVision). Randomization after patient inclusion prevents the possibility of recruitment bias (selection bias). Randomizing general practices rather than patients will avoid PCPs within a practice offering both Grip self-help and CAU, as this could cause contamination effects. Randomization will take place in blocks, randomly varying in size between 4 and 8, and a 1:1 allocation ratio.

### Control Group

Participants assigned to the control group will receive CAU during the study period. This could include care by the GP, GP-MHW, physiotherapist, and a psychologist. After the last follow-up measurement at 52 weeks, participants assigned to the control group will be offered access to the study intervention.

### Intervention Group

In addition to CAU, participants in the intervention group will be offered a Web-based self-help intervention called *Grip self-help*. Figure 2 shows a screenshot of the patient interface of the intervention.

The intervention comprises 2 steps. First, participants fill out a set of Web-based questionnaires concerning potential perpetuating factors: unhelpful cognitions, emotions, behaviors, and social factors associated with the physical symptoms. With this information, a personal problem profile is generated, identifying perpetuating factors that are relevant to the individual. Second, participants gain access to Web-based self-help exercises, selected using personalization algorithms based on their problem profile. Exercises are selected from a database, containing 59 unique exercises. Exercises include education, adjusting life style, identifying and challenging unhelpful cognitions, relaxation and mindfulness exercises, learning to accept the presence of physical symptoms and negative emotions, identifying values and setting goals accordingly, gradual exposure to feared activities, and managing the impact of symptoms on work and relationships. The exercises were not written from the perspective of a single therapeutic theoretical framework. Rather, they contain elements of cognitive behavioral therapy, acceptance and commitment therapy, and problem-solving treatment. The exercises vary with regard to duration (1 or 2 weeks) and intensity (varying from a single assignment to daily practice). Patients will work on 1 exercise at a time. The intervention will ultimately result in a personalized self-help guide, composed of texts that are extracted from the exercises patients found useful during the intervention.

The intervention is guided by the GP-MHW. A Web-based manual and technical support via email will be available to GPs and GP-MHWs allocated to the intervention group. These GPs and GP-MHWs will also be offered the option to take a free Web-based course on MUS and working with Grip.

GP-MHWs will be instructed to invite patients for at least two visits (start and finish). The frequency of further visits is left up to the GP-MHW. Although the exact length of the intervention will vary per person, we estimate that participating in the Grip self-help intervention on average takes 16 weeks. In 16 weeks, the participant will complete approximately 6 to 8 exercises.

